| 15      | 0                  | ... | ... | 0 | 0                     | 0 | 0 | 0 | 0 | 0 | 0 | 0 | 0 | 0 | 0 | 0 | 0 | 0 | 1 | 1 | 1 | 1 | 1 | 1 | 1 | 1 | 1                  | 1 | 1 |  |
| 16      | 0                  | ... | ... | 0 | 0                     | 0 | 0 | 0 | 0 | 0 | 0 | 0 | 0 | 0 | 0 | 0 | 0 | 0 | 0 | 1 | 1 | 1 | 1 | 1 | 1 | 1 | 1                  | 1 | 1 |  |
| 17      | 0                  | ... | ... | 0 | 0                     | 0 | 0 | 0 | 0 | 0 | 0 | 0 | 0 | 0 | 0 | 0 | 0 | 0 | 0 | 0 | 1 | 1 | 1 | 1 | 1 | 1 | 1                  | 1 | 1 |  |
| 18      | 0                  | ... | ... | 0 | 0                     | 0 | 0 | 0 | 0 | 0 | 0 | 0 | 0 | 0 | 0 | 0 | 0 | 0 | 0 | 0 | 0 | 1 | 1 | 1 | 1 | 1 | 1                  | 1 | 1 |  |
| 19      | 0                  | ... | ... | 0 | 0                     | 0 | 0 | 0 | 0 | 0 | 0 | 0 | 0 | 0 | 0 | 0 | 0 | 0 | 0 | 0 | 0 | 0 | 1 | 1 | 1 | 1 | 1                  | 1 | 1 |  |
| 20      | 0                  | ... | ... | 0 | 0                     | 0 | 0 | 0 | 0 | 0 | 0 | 0 | 0 | 0 | 0 | 0 | 0 | 0 | 0 | 0 | 0 | 0 | 0 | 0 | 1 | 1 | 1                  | 1 | 1 |  |

Retrospectively, 24 months of pre-measurements will be collected. The prospective data collection will include 20 months in which every month one cluster switches and 4 months of post-measurements. In the above a '0' indicates the control condition and a '1' the intervention condition.

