|-------------------------------------------------------------------------------|-----------------------------------------------------------------------------------------------------|--------------------------------------|------------------------------------------------------------------------|
| Change in mental health                                                       | Health-related Quality of Life (SF-36)                                                              | Score                                | Baseline
Surgery -1 week
Surgery +6 months
Surgery +12 months |
|                                                                               | Health-related Quality of Life (EQ-5D-5L)                                                           | Score                                | Surgery +6 months                                                      |
| Change in innate immune response
(only in abdominal aortic aneurysm group) | Degree of immunoparalysis                                                                           | Monocyte HLA-DR (mHLA-DR) expression | Baseline
Prior to anesthesia
Surgery +2 days
Surgery +6 weeks |
| Preoperative health behavior                                                  | Questionnaire for patients in control group

Questionnaire for patients in intervention group |                                      | Surgery -1 week                                                        |
| Intervention adherence                                                        |                                                                                                     |                                      | Surgery -1 week                                                        |
| Costs due to complications                                                    |                                                                                                     |                                      | Surgery +4 weeks                                                       |
| Costs due to length of hospital stay                                          |                                                                                                     |                                      | Surgery +4 weeks                                                       |

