### 10.2 Secondary study parameter(s)

All secondary data will be described by means plus SD per time point. Generalized linear models as described for the primary parameters will be used. This will be done by using the appropriate link-function (i.e. linear, log, logistic) and error-distribution (i.e, normal, binary). If data are continuous and non-normally distributed, data will be described by means plus IQR per time point. Categorical parameters will be described as number plus percentage per time point. Statistical methods will include t-test and Mann-Whitney U test for continuous normally respectively non-normally distributed parameters at a single time-point post-operatively. Categorical outcomes will be analyzed by using Chi-square tests or (logistic, ordinal or nominal, depending on the definition of the parameter) regression analysis for single time points.

For this section we consulted [name], department of Health Evidence, Radboudumc

The cost-effectiveness analysis will be performed from a healthcare perspective. The aim of the economic evaluation is to measure, value and analyze healthcare costs at a patient's level in patients undergoing usual preoperative care and patients undergoing a multimodal prehabilitation program. The time horizon of the economic evaluation is 12 months after surgery. The analysis will be performed along-side the stepped wedge trial with the primary outcome of the study (postoperative complications).

Standard cost prices for postoperative complications and both prehabilitation programs (PREHAB SHORT and PREHAB LONG) will be determined based on the 'Kostenhandleiding'(63). Data on costs due to postoperative complications will be collected throughout the study in Castor EDC. A multi-level generalized linear model (with gamma distribution and log-link function if data are non-normally distributed) will be used for the cost analysis with chosen fixed effects for time and random effects for clusters.

Additionally, a cost-utility analysis will be performed with quality-adjusted life-years (QALYs) based on the EQ-5D-5L at 6 months after surgery, following the Dutch guidelines of economic evaluation in healthcare(64).

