## 14. APPENDICES

### Appendix I: Overview of measurements

| OK -4w/OK -8w                                                                                                 | OK -1w                                                                              | OK | OK +1m                      | OK +6m                                                      | OK +12m                                            |
|---------------------------------------------------------------------------------------------------------------|-------------------------------------------------------------------------------------|----|-----------------------------|-------------------------------------------------------------|----------------------------------------------------|
| Screening
(in intervention group)                                                                   | Health behavior questionnaire                                                |    | Postoperative complications | Physical activity
- SQUASH questionnaire          | Physical activity
- SQUASH questionnaire |
| Physical fitness and activity
- submaximal Astrand test
- indirect 1RM
- SQUASH questionnaire | Physical fitness and activity
- submaximal Astrand test
- indirect 1RM |    | Length of stay              | Mental health
- SF-36 questionnaire
- EQ-5D-5L | Mental health
- SF-36 questionnaire      |
| Nutritional status
- length, body weight
- fat-free mass (BIA)
- 3-day food diary             | Nutritional status
- body weight
- fat-free mass (BIA)
- PG-SGA     |    |                             |                                                             |                                                    |
| Mental health
- SF-36 questionnaire                                                                 | Mental health
- SF-36 questionnaire                                       |    |                             |                                                             |                                                    |

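### The economic evaluation has a 12-month horizon, but the QALYs rest on one EQ-5D-5L at 6 months, so a 12-month QALY cannot be formed without assuming utility at the start and end

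*Protocol*

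**What the plan says.** Protocol section 10.2 states: "The time horizon of the economic evaluation is 12 months after surgery". The same section adds a cost-utility analysis with "quality-adjusted life-years (QALYs) based on the EQ-5D-5L at 6 months after surgery", following the Dutch guideline for economic evaluation. It gives no QALY formula, no shorter horizon for the cost-utility part, and no adjustment for baseline utility.

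The schedule agrees with the single time point:

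- Table 5 (section 8.1.2) has the row "Health-related Quality of Life (EQ-5D-5L") with 6 months after surgery as its only entry. The row sits under the shared outcome label "Change in mental health".
- Appendix I shows the EQ-5D-5L only in the 6-month column, as "SF-36 questionnaire - EQ-5D-5L".

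The SF-36 is scheduled more fully. Table 5 gives "Baseline Surgery -1 week Surgery +6 months Surgery +12 months", and Appendix I lists it in the same four columns. No section uses it to derive utilities.

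Two further statements bear on the point. Section 3 says of the control data: "Retrospectively, 24 months of pre-measurements will be collected". On costs, Table 5 places those of complications and of hospital stay at 4 weeks and cost-effectiveness at one year, while section 10.2 has complication-cost data gathered for the whole duration of the study.

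**The concern.** A QALY over a period is the area under the utility curve for that period. One observation in the middle fixes neither end of the curve. Someone has to supply the missing ends by assumption, and the incremental QALY, which is the denominator of the cost per QALY, then depends on that assumption.

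This is not a detail that the statistical analysis plan can settle. It can choose a model, but it cannot recover EQ-5D-5L values that the protocol's schedule never collects. Cost-effectiveness is a stated secondary objective in section 2, so a 12-month cost-utility result would be reported without the scheduled data to support it. Every patient who passes the baseline or 12-month contact without the EQ-5D-5L is lost to the simplest repair.

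**Working it through.** The protocol states no utility, QALY or cost-utility sample size, so there is no figure of its own to reproduce.

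**Inputs from the protocol**

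| Item | Value | Place |
|---|---|---|
| Horizon | 12 months after surgery | 10.2 |
| EQ-5D-5L | 6 months only | 10.2, Table 5, Appendix I |
| SF-36 | baseline, -1 week, 6 and 12 months | Table 5, Appendix I |
| Baseline contact | 4 or 8 weeks before surgery | Appendix I |

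**Weights.** With utilities u0, u6 and u12 at 0, 0.5 and 1.0 years, the trapezoid area is

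QALY = 0.5 × (u0 + u6)/2 + 0.5 × (u6 + u12)/2 = 0.25·u0 + 0.50·u6 + 0.25·u12.

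Only u6 is scheduled. The weight on unscheduled values is 0.25 + 0.25 = 0.50. Taken by interval, 0 to 6 months has no starting value and 6 to 12 months has no end value, so neither segment can be formed without an assumption.

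**Nodes.** The 0/6/12 grid is a convention chosen here, not the protocol's. Baseline falls before surgery, so placing it at time zero is an approximation. The value at -1 week lies nearer to surgery but follows prehabilitation in intervention patients.

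**What the missing ends can do.** The utilities below are assumptions. Take u6 = 0.80, u0 from 0.60 to 0.90 and u12 from 0.75 to 0.90.

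- Lowest: 0.25 × 0.60 + 0.50 × 0.80 + 0.25 × 0.75 = 0.7375.
- Highest: 0.25 × 0.90 + 0.50 × 0.80 + 0.25 × 0.90 = 0.85.
- Holding the 6-month value flat over the year: 0.80 in every case.

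**Difference between conditions.** The trapezoid contrast is 0.25·Δ0 + 0.50·Δ6 + 0.25·Δ12.

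- An assumed difference of 0.03 present only at 6 months gives 0.50 × 0.03 = 0.015 QALY, against 0.03 if held flat.
- An assumed starting imbalance of 0.02, 0.05 or 0.10 contributes 0.25 × Δ0 = 0.005, 0.0125 or 0.025 QALY to the trapezoid area. This is the part that adjustment for baseline utility addresses. It is not the error of a flat calculation, in which u0 has no weight.

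**A 6-month reading.** If the cost-utility analysis were meant to stop at 6 months, the area would be 0.5 × (u0 + u6)/2 = 0.25·u0 + 0.25·u6. Half of that weight (0.25 of 0.50) would still fall on the unscheduled starting value.

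**The case against.** Several stronger readings are tempting, and the protocol does not support them.

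- A reader might infer that the plan carries the 6-month utility across the year. No section says so. Section 10.2 gives no formula and refers to a guideline that is not at hand. What stands is that some assumption is needed.
- A reader might infer that differences in diagnosis mix pass straight into the cost per QALY. Diagnosis is the cluster. Section 10.2 applies the primary outcome's models, with fixed cluster effects, to secondary outcomes, and the cost model has random cluster effects. Such terms would absorb diagnosis mix. Within-cluster differences in baseline utility remain unseen.
- A reader might infer that baseline cannot be adjusted for at all. Baseline SF-36 is collected and could serve as a proxy covariate, and the choice of covariates may be left to the analysis plan. The gap is specific to EQ-5D-5L utility.
- A reader might infer that adding the missing time points would capture the early post-operative weeks. Neither questionnaire is scheduled between surgery and 6 months, so an early dip stays unmeasured either way.
- A reader might infer from Table 5 that costs stop at 4 weeks. Section 10.2 has complication costs collected throughout the study, so the two statements need reconciling. They do not show that later costs are missing.

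It is also fair to say that this is one additional secondary analysis and that the label for change in mental health is only a shared row heading. Both are accepted. Neither removes the mismatch between the horizon and the schedule.

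**Conclusion.** The point holds as a mismatch between horizon and measurement. Section 10.2, Table 5 and Appendix I agree on one EQ-5D-5L at 6 months, and section 10.2 sets 12 months. On a 0/6/12-month trapezoid, 50% of the weight falls on values not scheduled. That share depends on the chosen nodes, but the absence of a start and an end value does not. The utility examples only illustrate scale and rest on assumed values.

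A limit on any QALY comparison is that the 24 months of retrospective controls have no evident source for either questionnaire, so the comparison would rest on prospectively recruited patients.

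The primary outcome, its power and the complications-based effect measure are untouched. The change should be made because it is cheap and because the loss cannot be repaired once the contacts have passed.

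**What to change.** 1. Add the EQ-5D-5L at the existing baseline and 12-month contacts, where the SF-36 is already completed. Compute area-under-the-curve QALYs, adjusted for baseline utility, cluster and time. Cost: one short questionnaire twice per patient and a minor amendment.
2. For patients already past those contacts, or as a sensitivity analysis, derive preference-based utilities from the SF-36 at baseline, 6 and 12 months. Do not use the value at -1 week as the adjustment baseline, because it follows prehabilitation. Check first that the guideline the plan cites accepts this source. Cost: analysis wording plus that check, with no new data.
3. If neither is done, limit the cost-utility claim to what a single 6-month utility supports and do not report a 12-month cost per QALY.
4. State that the QALY comparison rests on prospectively recruited patients and that the early post-operative dip remains unmeasured.
5. Reconcile the 4-week cost rows in Table 5 with the 12-month horizon and with the collection of complication costs throughout the study. Cost: wording.

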### **10.3 Other study parameters**

Not applicable

### **10.4 Interim analysis**

Recruitment will be monitored. If the sample size per surgical cluster is fewer than expected, more pre-measurements may be retrospectively collected and more post-measurements prospectively. This assessment of recruitment will be done blinded, i.e. without testing the treatment effect.

## **11. ETHICAL CONSIDERATIONS**

### **11.1 Regulation statement**

This study will be conducted according to the principles of the Declaration of Helsinki (59th version, Seoul, October 2008) and other Dutch guidelines, regulations and Acts. Subjects will be coded by a numeric code in order to create an anonymous dataset. Investigators have access to this code and will store the subject identification code list at a separate location from the dataset. Data will be securely stored in the database of the department of surgery of the Radboudumc accessible to the investigators, in accordance with the Dutch Personal Data Protection Act.

### **11.2 Recruitment and consent**

Due to the fact that Dutch guidelines request that oncological patients should be operated within 5 weeks after diagnosis (unless neo-adjuvant therapy is indicated), the timelines for recruitment and informed consent are short to allow enough time for training. Therefore, patients undergoing high impact surgery in the Radboudumc will already be informed about the importance of preoperative condition and nutrition at the referral site. Written information, including the research subject information leaflet and the informed consent form, will be attached to the written invitation for the first outpatient clinic visit in the Radboudumc. Key points of the trial will be repeated during this first outpatient clinic visit. Either the surgeon or case manager will answer additional questions and ask if the patient is willing to participate in the trial by signing the informed consent form. If the patient agrees to participate in this trial, the surgeon or case manager will schedule an appointment (combined with a regular, preoperative outpatient clinic visit) for baseline measurements. Patients can contact an independent doctor (prof. dr. [name]) for any questions throughout the trial.

### **11.3 Objection by minors or incapacitated subjects**

Not applicable

### **11.4 Benefits and risks assessment, group relatedness**

As mentioned before, it is very likely that patients will benefit from the prehabilitation program intervention since they will be actively working on their physical, mental and nutritional health status. No minors and incapacitated subjects will be included in the study, due to the impossibility to perform all exercises and fulfill all questionnaires. Participating in this trial does not alter or delay the treatment in any way. Side effects might be exercise related problems. Exercise training is not expected to cause any risk to patients. However, since patients are thoroughly screened, we expect to find more pre-existing cardio-pulmonary conditions, for which patients will be referred to either a pulmonologist or cardiologist. The

amount of tests might be perceived as a burden for the patients in both groups, as well as the amount of hospital visits for the prehabilitation group for training and collecting data.

### **11.5 Compensation for injury**

The sponsor/investigator has a liability insurance which is in accordance with article 7 of the WMO.

The sponsor (also) has an insurance which is in accordance with the legal requirements in the Netherlands (Article 7 WMO). This insurance provides cover for damage to research subjects through injury or death caused by the study.

The insurance applies to the damage that becomes apparent during the study or within 4 years after the end of the study.

### **11.6 Incentives**

Participants will not receive a standard financial compensation for participation as an incentive. However, they will receive travel and parking compensation per prehabilitation visit (not the regular outpatient clinic visits) to the hospital.

## **12. ADMINISTRATIVE ASPECTS, MONITORING AND PUBLICATION**

### **12.1 Handling and storage of data and documents**

Data will be managed by an online data management system Castor EDC. Patients receive an unique study number, generated by the data management system. Study number is linked to patient details and stored in a secured file with password. Only the researcher has access to data.

### **12.2 Monitoring and Quality Assurance**

Monitoring will be performed via a risk-based approach, as recommended by the FDA. Although monitoring is legally not required for this study, the sponsor Radboudumc has decided to perform monitoring for all studies that fall under the scope of the WMO-act. Since this study has a minimal risk, monitoring should be performed annually and will partially be done centralized.

### **12.3 Amendments**

Amendments are changes made to the research after a favorable opinion by the accredited METC has been given. All amendments will be submitted to the METC that gave a favorable opinion.

### **12.4 Annual progress report**

The sponsor/investigator will submit a summary of the progress of the trial to the accredited METC once a year. Information will be provided on the date of inclusion of the first subject, numbers of subjects included and numbers of subjects that have completed the trial, serious adverse events/ serious adverse reactions, other problems, and amendments.

### **12.5 Temporary halt and (prematurely) end of study report**

The investigator/sponsor will notify the accredited METC of the end of the study within a period of 8 weeks. The end of the study is defined as the last patient's last visit.

The sponsor will notify the METC immediately of a temporary halt of the study, including the reason of such an action.

In case the study is ended prematurely, the sponsor will notify the accredited METC within 15 days, including the reasons for the premature termination.

Within one year after the end of the study, the investigator/sponsor will submit a final study report with the results of the study, including any publications/abstracts of the study, to the accredited METC.

## **12.6 Public disclosure and publication policy**

The trial is registered in the Netherlands Trial Register under code: NL8699. The research data will be published in relevant scientific journals. Authorship designations will be based on the recommendations of the International Committee of Medical Journal Editors (ICMJE).

## **13. STRUCTURED RISK ANALYSIS**

### **13.1 Potential issues of concern**

Not applicable

### **13.2 Synthesis**

Not applicable

## 14. APPENDICES

### Appendix I: Overview of measurements

| OK -4w/OK -8w                                                                                                 | OK -1w                                                                              | OK | OK +1m                      | OK +6m                                                      | OK +12m                                            |
|---------------------------------------------------------------------------------------------------------------|-------------------------------------------------------------------------------------|----|-----------------------------|-------------------------------------------------------------|----------------------------------------------------|
| Screening
(in intervention group)                                                                   | Health behavior questionnaire                                                |    | Postoperative complications | Physical activity
- SQUASH questionnaire          | Physical activity
- SQUASH questionnaire |
| Physical fitness and activity
- submaximal Astrand test
- indirect 1RM
- SQUASH questionnaire | Physical fitness and activity
- submaximal Astrand test
- indirect 1RM |    | Length of stay              | Mental health
- SF-36 questionnaire
- EQ-5D-5L | Mental health
- SF-36 questionnaire      |
| Nutritional status
- length, body weight
- fat-free mass (BIA)
- 3-day food diary             | Nutritional status
- body weight
- fat-free mass (BIA)
- PG-SGA     |    |                             |                                                             |                                                    |
| Mental health
- SF-36 questionnaire                                                                 | Mental health
- SF-36 questionnaire                                       |    |                             |                                                             |                                                    |

